# Efficacy and cerebral mechanism of acupuncture and moxibustion for treating primary dysmenorrhea: study protocol for a randomized controlled clinical trial

**DOI:** 10.1186/s13063-022-06675-1

**Published:** 2022-11-28

**Keywords:** Acupuncture, Moxibustion, Primary dysmenorrhea, Functional magnetic resonance imaging, Central mechanism

## Abstract

**Background:**

Acupuncture or moxibustion has been proven to be effective for patients with primary dysmenorrhea (PDM). However, the respective advantages and potential central mechanism of acupuncture and moxibustion are worthy of investigating to promote their further application.

**Methods:**

In this randomized controlled neuroimaging trial, 72 patients with PDM will be randomly assigned to three groups: acupuncture treatment group, moxibustion treatment group, and waiting list group. The acupuncture treatment group and moxibustion treatment group will receive acupuncture or moxibustion, respectively, for a total of 3 sessions over 3 consecutive menstrual cycles, and the waiting list group will not take acupuncture or moxibustion during these 3 menstrual cycles. The COX Menstrual Symptom Scale (CMSS), visual analog scale (VAS), and Pain Catastrophizing Scale (PCS) will be used to evaluate the clinical efficacy. The Self-rating Depression Scale (SDS), Self-rating Anxiety Scale (SAS), and 36-Item Short Form Health Survey (SF-36) will be used to assess the mental state and quality of life at baseline and at the end of treatment. Functional magnetic resonance imaging (fMRI) will be performed for detecting the cerebral activity changes at baseline and at the end of the treatment. The clinical data and imaging data will be analyzed among the groups. Correlation analysis will be conducted to investigate the relationship between brain functional changes and symptom improvement.

**Discussion:**

The application of the randomized controlled neuroimaging trial will provide objective and valid evidence about how acupuncture and moxibustion treatment relieve menstrual pain. The results of this study would be useful to confirm the potential similarities and differences between acupuncture and moxibustion in clinical efficacy and central mechanism for patients with PDM.

**Trial registration:**

Chinese Clinical Trial Registry ChiCTR2100043732. Registered on 27 February 2021

## Background

Primary dysmenorrhea (PDM) is one of the most common gynecological disorders with a prevalence of around 45–95% worldwidely [1]. It is characterized by recurrent, crampy, lower abdominal pain during menstruation in the absence of organic pelvic diseases [2, 3]. In some severe cases, patients may suffer from other symptoms including nausea, vomiting, limb cold, sweating, and even fainting accompanied by lower abdominal pain [4]. PDM significantly impacts the patients’ quality of life (QoL) and leads to high rates of school or work abence [5–8]. The current medical treatments for PDM range from nonsteroidal anti-inflammatory drugs (NSAIDs) to hormonal therapy [3, 7]. However, the side effects and unsatisfactory efficacy limit their clinical application [9–11]. Therefore, more and more doctors and patients are inclined to choose complementary alternative therapies.

Acupuncture and moxibustion are critical components of complementary alternative therapies and have good therapeutic effects on PDM [12, 13]. Acupuncture and moxibustion pertain to external therapies of traditional Chinese medicine (TCM). They are both guided by the traditional Chinese acupoint and meridian theory and functions in dredging the meridians and promoting the *qi* and blood circulation to treat diseases, although their procedures and manipulations are different. Acupuncture is to insert a needle into acupoints and impose a certain manipulation to achieve the purpose of treatment, while moxibustion is to place a burning mugwort directly or indirectly on acupoints to treat diseases. A number of studies had shown that whether acupuncture or moxibustion alone or a combination of both can relieve pain effectively to treat PDM [14–16]. Our previous studies have also verified the efficacy of moxibustion in alleviating menstrual pain and improving its related symptoms [13, 15]. In addition, previous studies have shown that the integration of the central system to acupuncture or moxibustion stimulation plays a crucial role in exerting the therapeutic effect [17, 18]. For example, researchers have found that both acupuncture and moxibustion improve cortex-subcortical coupling in remissive CD patients but through relatively different modulatory pattern [19]. Thus, although acupuncture and moxibustion are both effective in treating PDM, their respective advantages in effect and the underly mechanism remain unclear and need to be further investigated.

Therefore, we designed this randomized controlled neuroimaging trial aiming to (1) compare the therapeutic effects of acupuncture and moxibustion alone treating for PDM so as to investigate their respective advantages, (2) investigate the potential central mechanism of acupuncture and moxibustion for PDM using functional magnetic resonance imaging (fMRI), and (3) explore the potential correlations between cerebral activity changes and the improvement of clinical variables elicited by acupuncture or moxibustion.

## Methods/design

This is a randomized controlled paralleled neuroimaging trial. A total of 72 patients meeting the inclusion criteria will be recruited and randomly divided into three groups (the acupuncture treatment group, the moxibustion treatment group, and the waiting list group) by the ratio of 1:1:1 after a 3-month baseline period. Acupuncture and moxibustion treatment period will last for 3 menstrual cycles, while the waiting list group will not take acupuncture or moxibustion treatment during these 3 menstrual cycles. All patients will be allowed to use analgetic (VAS ≥ 8 cm), and the name, dose, and exact time of the medication will be recorded in the dysmenorrhea diary. Clinical outcome measurements and fMRI scan will be conducted at baseline and at the end of treatment. The study procedures are detailed in Fig. 1.

**Fig. 1 Fig1:**
[figure not shown]
Flowchart of the study. A total of 72 eligible patients with PDM will be randomly assigned to three groups: acupuncture treatment group, moxibustion treatment group, and waiting list group. Patients in the acupuncture treatment group and moxibustion treatment group will receive acupuncture or moxibustion, respectively, for a total of 3 sessions over 3 consecutive menstrual cycles, and the waiting list group will not take acupuncture or moxibustion during these 3 menstrual cycles. Both the outcome assessments and fMRI scan will be performed at baseline and at the end of treatment. The central mechanism of acupuncture and moxibustion in the treatment of PDM will be analyzed after data collection. fMRI, functional magnetic resonance imaging; PDM, primary dysmenorrhea

The study protocol conforms to the SPIRIT 2013 statement (Standard Protocol Items: Recommendations for Interventional Trials) [20]. The protocol has been approved by the Institutional Review Board of the Hospital of Chengdu University of Traditional Chinese Medicine (CDUTCM) (approved number: 2021KL-010) and registered at Clinical Trial Registry (registration number: ChiCTR2100043732).

### Participants and recruitment strategy

Patients will be recruited from the outpatient clinic in the Gynecology Department of the Affiliated Hospital of CDUTCM and the campus of CDUTCM. The recruitment strategy mainly includes posting advertisement, delivering leaflets, and distributing information on WeChat (the largest social media platform in China). All patients will be informed of the study procedures, potential benefits, and risks, and written informed consent will be obtained before the allocation.

### Inclusion criteria

Patients fulfilling the following criteria will be included: (1) nulliparous women aged 18–30 years old, (2) right-handed, (3) meeting the diagnostic criteria of PDM under the Primary Dysmenorrhea Consensus Guideline [21], (4) having regular menstrual cycles (28 days ±7 days), (5) having an average score of the menstrual pain visual analog scale (VAS) of at least 4 cm (range of 0 to 10 cm) during the last menstrual period, and (6) having signed informed consent form.

### Exclusion criteria

Patients matching any of the following criteria will be excluded: (1) having been diagnosed with secondary dysmenorrhea caused by polycystic ovarian syndrome, endometriosis, uterine myoma, or other gynecological problems confirmed by B-ultrasound and gynecological examination, (2) having MRI contraindications such as severe claustrophobia, pacemakers, or implanted ferromagnetic metal, (3) experiencing severe depressive or anxiety disorder, (4) complicating with life-threatening diseases such as psychiatric, neurologic, cardiovascular, cerebrovascular, liver, kidney, and hematopoietic system illnesses, (5) being pregnant or lactating or preparing to be pregnant, (6) using analgesics and sedatives 2 weeks prior to enrollment, and (7) participating in other clinical trials.

### Sample size

According to the statistical requirements of neuroimaging studies, 12–15 individuals in each group is the reasonable sample size for stable cerebral responses [22, 23]. Considering a drop-out rate of 20% and possible excessive head motion during scanning, a sample size of 24 in each group is required, and a total of 72 PDM patients will be recruited.

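### The sample size rests on an imaging rule of thumb with an unquantified scan loss; it does not support the clinical acupuncture–moxibustion comparison, and the planned difference tests cannot establish similarity

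*Protocol article*

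**What the plan says.** The whole justification is in the protocol article under Sample size. It takes as its base that "12–15 individuals in each group is the reasonable sample size for stable cerebral responses". It then allows for losses and states the result: "Considering a drop-out rate of 20% and possible excessive head motion during scanning, a sample size of 24 in each group is required", hence 72 in total. Methods/design gives 1:1:1 allocation. The section names no clinical endpoint, effect size, SD, power or precision.

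The Background lists three aims. The first is to "compare the therapeutic effects of acupuncture and moxibustion alone treating for PDM so as to investigate their respective advantages". The other two concern the central mechanism and the correlation of brain changes with clinical improvement.

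The Discussion part of the abstract says the results would be useful to "confirm the potential similarities and differences between acupuncture and moxibustion in clinical efficacy and central mechanism". The opening of the main Discussion and the strengths and limitations section also speak of similarities together with differences.

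Clinical data analysis specifies intention-to-treat analysis with imputation, repeated measures ANOVA on pre- and post-treatment data, Šidák-corrected comparisons between groups, two-sided tests and a 0.05 threshold. It gives no equivalence margin and no test of equivalence.

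**The concern.** Two things do not fit together.

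First, the size is presented as a requirement, but its basis concerns cerebral responses only. It does not bear on the clinical comparison of two active treatments, which is the first aim. One of its two loss allowances has no figure, so a reader cannot reproduce 24.

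Second, the article raises the prospect of confirming similarities, while every clinical test it describes looks for a difference. Failing to reject a null hypothesis of no difference is not evidence of similarity, least of all when the comparison is imprecise. With this size, a non-significant acupuncture–moxibustion result could easily arise even if the treatments differ by a moderate amount. The plan contains nothing to stop that result being reported as similar efficacy or a shared mechanism.

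**Working it through.** **1. The plan's own figure**

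Inputs from Sample size: base 12–15 per group; drop-out 20%; head-motion loss named without a figure. Formula: n / (1 − drop-out).

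- 12 / 0.80 = 15
- 15 / 0.80 = 18.75, rounded up to 19

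The quantified inputs give 15–19 per group, or 45–57 in total, against the stated 24 and 72. The remainder must be head motion. Of 24 patients, 24 × 0.80 = 19.2 remain after drop-out, so the largest further scan loss that still leaves the base is:

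- base 15: 1 − 15/19.2 = 21.9%
- base 12: 1 − 12/19.2 = 37.5%

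In the other direction, a 20% scan loss on top of drop-out gives 15 / (0.80 × 0.80) = 23.4, rounded up to 24. So 24 can be reached with a plausible loss, but the text does not fix which loss was used.

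**2. What the size gives for the first aim**

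The document states no effect size, SD or power for this comparison. Assumptions:

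- Differences are in SD units and target power is 80%.
- The test is an unadjusted two-sample t-test.
- Šidák covers the three pairwise comparisons: alpha = 1 − 0.95^(1/3) = 0.01695. The document gives the method but not the number of comparisons, so alpha 0.05 is shown as well.
- There are 24 per arm (all randomised) or 19 per arm (24 × 0.80 = 19.2).

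Power comes from the non-central t distribution with 2n − 2 degrees of freedom and non-centrality d × √(n/2). The 95% CI half-width is t(0.975; 2n − 2) × √(2/n).

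| | 24 per arm | 19 per arm |
|---|---|---|
| Detectable difference, Šidák | 0.96 SD | 1.09 SD |
| Detectable difference, alpha 0.05 | 0.83 SD | 0.93 SD |
| Power at assumed d = 0.5, Šidák | 24% | 18% |
| Power at assumed d = 0.5, alpha 0.05 | 40% | 32% |
| 95% CI half-width | 2.013 × 0.289 = 0.58 SD | 2.028 × 0.324 = 0.66 SD |

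**3. Effect of using the baseline**

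Baseline adjustment multiplies the SD by √(1 − r²), where r is the baseline–post correlation. The document gives no r; 0.5 to 0.7 is assumed. At 24 per arm:

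- r = 0.5: factor 0.866; detectable difference with Šidák 0.96 × 0.866 = 0.83 SD; half-width 0.58 × 0.866 = 0.50 SD
- r = 0.7: factor 0.714; detectable difference with Šidák 0.96 × 0.714 = 0.69 SD; half-width 0.581 × 0.714 = 0.415, about 0.42 SD

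**4. Similarity**

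The usual equivalence procedure is two one-sided 5% tests, which amounts to asking whether the 90% CI lies inside the margin. At 24 per arm the unadjusted 90% half-width is 0.485 SD. If the true difference is zero, power at 24 per arm is about 8% for an assumed margin of 0.5 SD and about 92% for 1.0 SD. What the trial could show therefore depends almost entirely on the margin, and none is stated.

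**The case against.** The strongest reply has four parts.

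*The 24 is not wrong.* The section names head motion as a second allowance, and a scan loss of about 20% after drop-out takes 15 to 24. This stands. A reader might infer an arithmetic error, but the document supports only a missing input. Nor should anyone write in 22% for the sponsor: that figure follows from a base of 15, and a base of 12 gives 37.5%.

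*Scan losses do not remove clinical data.* Excessive head motion costs images, not pain or symptom scores, and the clinical analysis is intention-to-treat with imputation. This stands, and it is why the working uses 24 and 19 per arm and nothing smaller.

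*The planned model uses the baseline.* An unadjusted t-test is pessimistic. This stands in part: at 24 per arm the detectable difference with Šidák falls to about 0.83–0.69 SD, so a figure near 1 SD should not be written into the protocol as fact. It still leaves a moderate difference of 0.5 SD below what the trial can detect with 80% power.

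*No conclusion of similarity is announced.* The abstract says only that the results would be useful to confirm potential similarities and differences, and elsewhere the text speaks of comparing or investigating. Nothing says that P > 0.05 will be read as similar. This stands, so the point is about what the plan leaves open and not about a declared misuse.

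Two further readings go too far. One is that equivalence is out of reach at this size: that depends on the margin, and a wide one would be feasible. The other is that the imaging rule applies only to mapping a single group: that would rest on the cited sources, which are not at hand, and the section itself says only "individuals in each group is the reasonable sample size for stable cerebral responses".

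**Conclusion.** The concern holds in this form. The size is called required on an imaging rule plus 20% drop-out and a head-motion loss without a figure; the quantified part reaches 15–19, and the section offers no support for the clinical comparison that is the first aim. Because the article plans only tests of difference and states no margin, a non-significant acupuncture–moxibustion result could not establish similarity of efficacy or mechanism.

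The size of the problem is illustrative, since every effect size, margin, correlation and power level above is an assumption. Without adjustment and with Šidák over three comparisons, a true difference of 0.5 SD would be missed about three times in four at 24 per arm. Dropping Šidák or adjusting for baseline improves this. The conclusion about similarity does not rest on any of these numbers; it follows from the absence of a margin.

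**What to change.** Keep 72 patients and change the wording.

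- In Sample size, say that the number was set on imaging grounds and that the trial was not powered for the clinical comparison. Give the base actually used and the scan-loss rate actually assumed; only the sponsor can supply these.
- In Clinical data analysis, report acupuncture versus moxibustion as a baseline-adjusted difference with a 95% CI, and state the expected precision with its assumptions (SD, baseline correlation, number of Šidák comparisons).
- In the abstract, replace "confirm the potential similarities and differences between acupuncture and moxibustion in clinical efficacy and central mechanism" with wording about estimating the difference between the two treatments, and align the parallel sentences in the Discussion and in the strengths and limitations section.
- Add a sentence that P > 0.05 will not be read as similar efficacy or mechanism unless an equivalence margin is pre-specified.

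The cost is drafting time only: no added patients, visits or scans. The downside is that the stated claims and precision become less favourable.

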### Randomization and blinding

Randomization will be implemented using computer-generated randomization digital table which is created by Excel’s rand function. Seventy-two eligible PDM patients will be randomly assigned to the acupuncture group, moxibustion group, and waiting list group (1:1:1 ratio). Random information will be put into an opaque, sealed envelope and saved by those who will not participate in the study. Due to the particularity operation of acupuncture and moxibustion, it is difficult to blind operators and patients. However, outcome assessors and statisticians were blinded to the procedure and the result of randomization, group allocation, and intervention to reduce the risk of bias.

### Interventions

#### Acupuncture interventions

Patients in this group will receive manual acupuncture at CV4 (Guan yuan) and SP6 (San yinjiao) with disposable sterile filiform needles (0.25 × 40 mm, Huatuo Medical Instrument Co., Ltd., China). Based on our previous studies and academic literature data mining, these acupoints have been proven to be effective and most frequently used for PDM [13, 24, 25]. Needles will be perpendicularly inserted into the acupoints at a depth of 20–30 mm after skin disinfection using alcohol; acupuncturists will then bi-directionally twist the needles by 90–180°, lifting and thrusting the needles with the amplitude of 3–5 mm for 1–1.5 Hz to induce *Deqi* sensation. After the *Deqi* sensation is attained, the needles will be retained at the acupoints for 30 min.

#### Moxibustion treatment

Patients in this group will receive mild moxibustion at CV4 and SP6 with moxa sticks (Z32021062, Oriental Moxa Co., Suzhou, China). The moxa sticks are made of moxa floss and are cylindrical, with a diameter of 1.5 cm and a length of 20 cm. The ignited moxa sticks will be applied approximately 2–3 cm above the dermal layer of the acupoints to produce a mildly warm and comfortable sensation that is similar to a *Deqi* sensation in acupuncture. Moxibustion at each point commonly lasts for about 10–15 min [13].

Patients will receive acupuncture or moxibustion treatment 5 days before the onset of menstruation, once a day, 5 days a session for a total of 3 sessions over 3 consecutive menstrual cycles. All the acupuncture and moxibustion manipulation will be performed by two licensed acupuncturists with at least 3 years of clinical experience.

### Waiting list group

Patients in the waiting list group will not receive acupuncture or moxibustion intervention and only need to maintain their previous habits. The participants will also complete the examination and evaluation at the corresponding time point. Considering the ethical requirements, all patients in this group will receive free acupuncture or moxibustion treatment at the end of the trial.

### Measurements

The measurements mainly include basic information collection, symptom measurement, and neuroimaging scanning assessments. All measurements will be performed independently by trained assessors. The study schedule is exhibited in Table 1.

**Table 1 Tab1:** Study schedule of enrollment, intervention, and assessments

	Baseline	Allocation	Treatment		
Time point	− 3 months	0 months	1 month	2 months	3 months
**Enrollment**					
Eligibility screen	√				
Informed consent	√				
Demographics	√				
Medical history	√				
Physical examination		√			
Randomization		√			
**Interventions**					
Group A (acupuncture)			√	√	√
Group B (moxibustion)			√	√	√
Group C (waiting list)			√	√	√
**Assessments**					
MRI scans		√			√
VAS		√	√	√	√
CMSS		√	√	√	√
PCS		√	√	√	√
SAS		√			√
SDS		√			√
SF-36		√			√
**Participants safety**					
Adverse events			√	√	√

### Demographic and basic clinical information collection

The demographic information including name, age, height, weight, level of education, and history of PDM and other concomitant diseases will be collected at the baseline. The vital signs including blood pressure, pulse, respiration rate, and temperature will also be measured.

### Symptoms measurement

#### The COX menstrual symptom scale (CMSS)

The CMSS is commonly used to evaluate dysmenorrhea symptoms and other accompanying symptoms [26]. The scale contains 18 symptom items, each of which includes both total onset time and average severity.

#### Visual analog scale (VAS)

The VAS is a tool widely used to measure pain intensity [27]. Patients will be asked to indicate a perception of pain intensity scored from 1 to 10 (0 = no pain sensation, 10 = the worst pain sensation) along a 100-mm horizontal line.

#### Pain catastrophizing scale (PCS)

The PCS is a 13-item self-report tool used to assess an exaggerated negative orientation towards actual or anticipated pain experiences [28, 29]. The scale measures different features of pain catastrophizing from three subscales: rumination, magnification, and helplessness.

#### Psychological state assessment

The Self-rating Anxiety Scale (SAS) and Self-rating Depression Scale (SDS) will be used to evaluate the emotional state [30, 31].

#### Measurements for the quality of life

The 36-item Short Form Health Survey (SF-36) will be used to evaluate the quality of life [32]. The scale contains 8 dimensions including physical functioning, role limitations due to physical health problems, role limitations due to emotional problems, social functioning, bodily pain, vitality, mental health, and general health.

The VAS, CMSS, and PCS will be measured at baseline and every menstrual cycle throughout the treatment. The SAS, SDS, and SF-36 will be measured at baseline and at the end of the treatment.

